### Sample Size Calculation

For a main trial designed with 90% power and two-sided significance level of at least .05, a pilot sample size of 25 per arm is needed to detect a small effect size of 0.2 in the primary outcome measure [55]. A meta-analysis suggested that many high-quality psychotherapy studies (high quality studies defined by a proficiently trained therapist, treatment integrity, N>50) on the treatment of depression have a mean effect size of 0.22 [56]. Allowing for an attrition rate of 30% at follow-up (a larger estimate due to end-of-life context), the sample size must be inflated by a factor of 1/(1−0.3)=1.43. Therefore, the minimum sample size required for this study was 72 or 36 in each group.

### Recruitment Procedures

Purposive sampling was adopted to achieve a target sample size of 72. Potential participants are identified and contacted by the collaborating organization (leading pediatric palliative care providers in Singapore, including KK Women’s and Children’s Hospital, Club Rainbow Singapore, Muscular Dystrophy Association Singapore, and Rare Disorders Society Singapore) to introduce the study to their beneficiaries. This sampling strategy allows the recruitment of participants whose children suffer from a wide range of chronic life-threatening conditions, thus allowing for maximum variation in the sampling. If verbal consent is obtained from potential participants, their contact details are passed to the research team at Nanyang Technological University, who subsequently establish telephone contact, explain study procedures, and introduce the NeW-I web-based platform. All personal information pertaining to potential participants are kept confidential, and only the responsible researchers have access to such information.

Open recruitment is also carried out so that all parents of children with chronic life-threatening illnesses have equal opportunity to participate in a potentially beneficial study and to examine the feasibility of implementing this free and easily accessible intervention in the community. Posters have been placed in strategic locations across Singapore (such as offices of leading pediatric palliative care providers) that provide information regarding the study. When interested participants contact the research team, the study procedures are explained, the NeW-I platform is introduced, and registration information is provided.

### App and Intervention Procedure

The NeW-I therapist-facilitated web-based platform comprises a mobile app and a website (both of which have the same content and functionality). Participants can download the app free of cost from the Apple App Store and the Google Play Store by keying in the relevant keywords or scanning the quick response code provided on the NeW-I study advertisement posters. The NeW-I website is under construction. As shown in Multimedia Appendix 1, when participants initially log in to the app, they are directed to a study participation and informed consent page that provides details about study procedures, institutional affiliations of the research team, rights of research participants, and protection of confidentiality. After participants endorse this web-based informed consent form on the NeW-I platform, they are directed to a demographic information page. Participants are also requested to provide their contact details and last few digits of their national identification number to ensure that only 1 user account is created by each individual.

Following this, participants are directed to a screening page where participants complete the PHQ-9 and the K-10. Those who pass the screening assessments receive confirmation of study participation and are requested to wait for a phone call from the research team. Those who do not pass the screening assessments are thanked for their time and provided with resources for psychosocial support. Individuals who pass the screening assessments receive a phone call from the NeW-I team as a means of identity checking. Following this, participants complete baseline measures (time point 1 assessment). This is followed by a random allocation of participants to either the intervention group or the control group, which is performed via the NeW-I platform using computer-generated random numbers. Participants are then directed to the first writing session. Participants have the option to choose to begin the first writing session immediately or delay for a maximum of 3 days. The day on which participants begin their first writing session is day 1 of week 1. Participants who do not begin their first writing session within 3 days are excluded from the study. However, a concession period of 7 days is given to participants who have a genuine reason for their inability to adhere to the protocol (such as unexpected changes in their child’s health condition) and have expressed keen interest in participating in the study. A similar concession period of 7 days is also maintained for participants who are unable to adhere to the study protocol in weeks 2, 3, and 4 (such that each participant can only be given 1 concession during the entire duration of their study participation). Detailed study procedures are described in Figure 2.

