## Methods

### Study Design and Hypotheses

This study utilizes an open-label randomized controlled trial design comprising 2 groups: (1) an intervention group (structured NeW-I protocol) and (2) a control group (journaling activity unrelated to their child’s illness). It is hypothesized that intervention participants who successfully complete NeW-I will experience an enhanced quality of life, spiritual well-being, sense of hope, and perceived social support and decreased depressive symptoms, subjective caregiver burden, and risk of complicated grief as compared with control participants. It is also hypothesized that NeW-I is deemed as an accessible and user-friendly service by participants.

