### Data Analysis

#### Quantitative Data

The statistical analysis plan for the quantitative data in this study was designed according to the Consolidated Standards of Reporting Trials guidelines [64] and recommendations made by Gamble et al [65] for clinical trials. Quantitative parameters will be presented as mean (SD) or median (IQR), and categorical variables will be presented as numbers and proportions. The internal consistency of psychometric scales will be assessed using Cronbach alpha. To compare the primary quantitative outcome (KQOL) and secondary quantitative outcomes (FACIT-Sp-12, HHI, PHQ-9, BSFC-s, ISS, and BGQ) between the intervention and control groups over time (time point 1 to time point 5, with time point 2 being the primary time point of comparison), multilevel mixed-effect regression analysis will be used with time as a random effect. All demographic and other relevant covariates measured at baseline will be adjusted in the model. Mixed models allow us to include all available data in the presence of dropouts occurring into the analysis [66]. Individual multivariable models will be constructed for each outcome to estimate the effect sizes and corresponding CIs. Clinically meaningful interactions will also be checked and included in the model if *P*<.10. Marginal effects will be used to predict mean outcome scores for the intervention and control groups. For this study, a two-sided significance level of at least .05 will be considered a statistically significant finding. All analyses will be conducted using Statistical Package for the Social Sciences (SPSS) (version 22.0; IBM Corp) and Stata (version 15.1; StataCorp) statistical software.

The intention-to-treat principle will be followed in the data analysis. However, an additional sensitivity analysis will be conducted to handle missing data during the analysis, where fully conditional multiple imputation with *n (% missing)* imputations and 1000 iterations using the Markov Chain Monte Carlo method will be used [67]. Model summary estimates will be calculated based on the Rubin rule [68].

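### Randomised parents who do not start writing within 3 days are excluded, leaving them with no primary outcome and undermining the stated intention-to-treat analysis

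*Protocol article*

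**What the plan says.** The order of events is in the protocol article, App and Intervention Procedure. Participants are screened, telephoned for an identity check, and complete the time point 1 measures. Then: "This is followed by a random allocation of participants to either the intervention group or the control group". After allocation, "Participants are then directed to the first writing session", and "Participants have the option to choose to begin the first writing session immediately or delay for a maximum of 3 days". The consequence of a longer delay is stated at once: "Participants who do not begin their first writing session within 3 days are excluded from the study".

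The rule is softened by a concession: "a concession period of 7 days is given to participants who have a genuine reason for their inability to adhere to the protocol". An unexpected change in the child's health is the example given, and the parent must also have shown keen interest in taking part. Only one concession is allowed per participant over the whole study.

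The Quantitative Data section under Data Analysis says: "The intention-to-treat principle will be followed in the data analysis". It names time point 2 as the primary time point of comparison and plans mixed models on all available data, with multiple imputation as a sensitivity analysis. Study Design and Hypotheses describes the trial as open label and words the hypothesis around completers: "It is hypothesized that intervention participants who successfully complete NeW-I will experience an enhanced quality of life".

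The Sample section has a related rule. Participants who cease to meet the inclusion criteria, for example because the child dies, are excluded, but the data collected up to then are kept and analysed. No comparable sentence covers parents who do not start writing.

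**The concern.** Intention to treat needs two things: everyone randomised is analysed in the allocated arm, and outcomes are sought from everyone whether or not they took up the intervention. The 3-day rule works against both, because it acts after allocation and depends on the participant's behaviour.

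The two arms need not lose the same people. The trial is open label, and the week 1 tasks differ: intervention parents write about their child and the challenges of caregiving (Table 2), control parents about an average day (Table 3). The concession is a judgement made after allocation, with no stated blinding. If non-starting relates to quality of life and occurs at different rates or for different reasons in the two arms, the remaining groups are no longer comparable by randomisation. Outcomes that were never collected cannot be recovered by any later analysis plan.

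**Working it through.** **1. The plan's own figure.** Sample Size Calculation gives 25 per arm, inflated for 30% attrition: 25/(1 − 0.3) = 35.7, rounded up to 36 per arm and 72 in total. This reproduces the stated number. The 25 comes from a cited source and is taken as given. The proposed fix does not change it.

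**2. Is the exclusion after randomisation?** Yes. The sequence is baseline, allocation, direction to session 1, then a wait of up to 3 days. The deadline concerns a session that comes after allocation.

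**3. What data would a non-starter contribute?**
- Removed from the analysis: none, and intention to treat fails outright.
- Participation ended but data kept, by extension of the Sample section: one baseline value. Time points 2 to 5 are all missing, so the mixed model has no observed primary outcome for that person, and imputation must supply it from baseline under an assumption about why it is missing.

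On either reading the protocol itself stops collection from parents who might have answered.

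**4. How large could the effect be?** The article gives no non-start rate, so the following are assumptions. The quantity is the shift in an unadjusted comparison of starters only, with no true effect.

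- Model A: excluded parents would score 0.5 SD below starters. Bias = (q_I − q_C) × 0.5, where q_I and q_C are the excluded fractions in the intervention and control arms.
- Model B: a normal propensity to start has correlation ρ with the outcome, and the lowest fraction q is excluded. The mean of those kept is ρ·φ(z_q)/(1 − q); bias is the difference between arms.

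| Excluded, one arm vs other | Number of 36 | Model A | Model B, ρ = 0.3 | Model B, ρ = 0.5 |
|---|---|---|---|---|
| 5% vs 5% | 1.8 vs 1.8 | 0 | 0 | 0 |
| 10% vs 5% | 3.6 vs 1.8 | 0.025 | 0.026 | 0.043 |
| 15% vs 5% | 5.4 vs 1.8 | 0.050 | 0.050 | 0.083 |
| 20% vs 10% | 7.2 vs 3.6 | 0.050 | 0.046 | 0.077 |
| 20% vs 5% | 7.2 vs 1.8 | 0.075 | 0.072 | 0.121 |
| 30% vs 10% | 10.8 vs 3.6 | 0.100 | 0.091 | 0.151 |

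Values are in SD. The sign favours whichever arm loses more people, if those lost would have scored lower; swapping the arms reverses it.

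**5. Scale.** Against the 0.2 in Sample Size Calculation, 0.025 is 0.025/0.2 = 12.5% and 0.151 is about 76%. Against the pilot's own precision, with 25 completers per arm the unadjusted standard error of the difference is √(2/25) = 0.28 SD, so the same range is about 9% to 53% of one standard error.

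**The case against.** **Flat contradiction.** A reader might infer that the rule deletes non-starters from the analysis and so cannot stand beside intention to treat. The article does not say that. In the Sample section, exclusion goes together with keeping and analysing the data already collected, so the word can mean the end of participation. The mixed model and the imputation could also carry a non-starter with baseline only. This part of the objection stands. But the retention sentence is written for participants who cease to meet the inclusion criteria, and extending it still leaves no outcome at time point 2.

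**Parents in crisis are the ones lost.** A reader might infer this too. The concession points partly the other way, since a change in the child's health is its own example of grounds for more time. Severe depressive symptoms and distress are screened out before allocation.

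**Uptake and retention look inflated.** The Acceptability and Feasibility Study section keeps an audit trail of uncompleted interventions with reasons, and of protocol deviations. Non-starters may well appear there. The audit would not supply their outcomes.

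**Bias in favour of NeW-I.** This is not supported. It requires more exclusions in the intervention arm, of parents who would have scored lower; nothing in the article shows either. Nor does the article say that the prompts are seen before a participant chooses to start or delay; Figure 2 and the app screenshots, which might settle this, are not shown.

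**Size.** Every rate, gap and correlation above is assumed. If baseline values are kept, a model that uses them may reduce the shift.

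**Conclusion.** The point holds in a limited form. The rule as written removes randomised participants on post-randomisation behaviour, and no sentence keeps them in follow-up or in the analysis. Even on the kindest reading they have no observed primary outcome, so the intention-to-treat statement could not be carried out in full for them.

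Arm-dependent selection is made possible, not shown, and its size and direction are unknown. The 0.03 to 0.15 SD range describes a starters-only comparison under assumed exclusion differences of 5 to 20 percentage points and the assumed link between starting and outcome. Equal exclusion by the same mechanism gives zero.

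For a pilot this size the shift would be smaller than the sampling error. It still merits correction because objective 2 is to evaluate efficacy, the results are to inform a full-scale protocol, and uncollected outcomes cannot be restored.

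**What to change.** Replace the exclusion sentence with a rule that every randomised participant:
- stays in the allocated arm in the intention-to-treat set;
- is invited to complete the questionnaires at time points 2 to 5, whether or not writing begins;
- if writing never begins, is reported as a non-starter by arm, with reasons.

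Time points 2 to 5 are defined from completion of the protocol, so the rule must also give non-starters a date from which these are counted. Concessions granted and refused should be reported by arm.

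**Cost.** Each assessment carries a S$30 voucher, so four cost 4 × 30 = S$120 per non-starter. If 10% of 72 did not start (about 7 people, assumed), that is at most 7 × 120 = S$840. The effect estimate may be diluted: with 10% non-starters who gain nothing, 0.2 becomes 0.9 × 0.2 = 0.18. The sample size of 72 is unchanged.

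Triggering allocation at the moment a participant begins session 1 is an option for a future main trial. It would mean that late starters are never randomised, at the price of losing uptake data by arm. It is less suitable here, since recruitment is already under way and the change would alter the randomisation procedure mid-trial.

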**Figure 2 figure2:**
[figure not shown]
Description of Narrative e-Writing Intervention (NeW-I) procedures.

NeW-I is delivered by trained therapists in the research team who are experts in death education and grief counseling and have the clinical competence to work with family caregivers in pediatric palliative settings. All team members have successfully completed research integrity modules under the provisions of Nanyang Technological University’s institutional review board and adhere to the board’s guidelines for safeguarding participants’ identity and confidentiality.

### Intervention and Control Groups

Both intervention and control group participants follow the procedures described in Figure 2. There are 4 weekly sessions of writing. A template has been provided to ensure that the participants’ writings tie in with the session objectives. To improve participants’ adherence to the study protocol, they receive an automated notification on their phone app and email each time a fresh writing session becomes available to them. Participants were assured of anonymity and confidentiality of their writing to encourage open and honest self-expression. The structured writing for each session requires 15 to 30 min, as exposure and time to process ideas through written disclosure over at least three sessions of 15 min each can produce effective outcomes [57].

For the intervention group participants, each weekly session has a unique objective (Table 2). Briefly, in week 1, participants reflect on the demands of caring for a child with a chronic life-threatening illness and the means to cope with these challenges. In week 2, participants consider avenues where they could seek more information about their child’s illness and resources for caregiving. In week 3, participants examine the sources of support that they have within their network of family and friends. In week 4, participants explore how they (and their children) could rise above illness-related challenges and live their lives as fully as possible.

For control group participants, the objective is consistent across the 4 weeks, that is, participants engage in a weekly writing session that is unrelated to their child’s illness and allows them to experience the therapeutic benefits of narrative writing (Table 3).

**Table 2 table2:** Content and questions for reflective writing for intervention group.

Session structure	Week 1	Week 2	Week 3	Week 4
Objective	To provide participants with a platform to reflect on the emotional, practical, and financial demands of caring for a child with a chronic life-threatening illness and the means to cope with these challenges.	To explore avenues where participants can seek more information about their child’s illness and resources for caregiving.	To explore the sources of support that participants have within their close network of family and friends.	To explore how participants (and their children) can rise above illness-related challenges and live their lives as fully as possible.
Questions for reflective writing	Tell us a little about your child and what you love about him or her. Tell us about the challenges that you have encountered when caring for your child. What has been your biggest challenge so far? How have you coped with it? What are three things that have helped you cope in your caregiving journey?	How satisfied are you with the knowledge and information that you have about your child’s condition? What has been helpful in providing you with the knowledge and information? What are some forms of support that have been helpful for you in providing quality care to your child? How were these forms of support helpful? What would help you to feel more competent as your child’s caregiver? What is one thing you could do to make that difference?	Tell us about some people who have been helpful or supportive in your caregiving journey. How have they helped you to cope during difficult times? On a scale of 1 to 10, with 1 being “Not at All” and 10 being “Very Much,” how satisfied are you with your spousal relationship? (Please omit this question if it does not apply to you.) What might make that score a little higher? What are some things that others could do for you that could further help you in your caregiving journey?	Tell us what you love best about your child. What quality about him or her makes you proud? What would a good day for your child look like right now? What makes it a good day? Tell us about an enjoyable moment with your child. What are some things you can do to make an enjoyable moment happen?
Counseling goals	To affirm the strengths that have helped participants to survive and thrive. To provide psychoeducation about local social welfare organizations that can provide them with support.	To acknowledge participants’ efforts to seek power and control over their seemingly uncontrollable lives through illness literacy. To provide psychoeducation about sources for seeking more information about their child’s illness, treatment options, and resources for caregiving.	To reframe that they are indeed blessed to have the support of their spouse or family or friends to help them to cope with this challenging period. To reframe participants’ sharing from sessions 1, 2, and 3 by taking the semantic content as it is but providing an alternative viewpoint of perceiving the situation.	To assist participants (and their children) in building meaningful and cherished memories through reflecting on achievements and fulfillment of dreams. To examine ways in which participants can enhance quality of life in their child’s final days.

**Table 3 table3:** Content and questions for reflective writing for control group.

Session structure	Week 1	Week 2	Week 3	Week 4
Questions for reflective writing	This week, we’d love to know a little bit about you. Tell us what an average day in your life looks like. Feel free to share with us any and every detail that you find comfortable to talk about!	This week, we’d like to know about what has the past week been like for you? Feel free to share with us in as much detail as you like!	This week, we’d like to know what is the biggest challenge (e.g. emotional, financial, practical etc.) that you are facing right now? Do feel free to add on anything else about this challenge that you would like us to know!	This week, we’d like to know what you find most comforting right now (e.g. family, relationships, work, hobbies and other activities etc.). Tell us about what makes this thing comforting for you?

### Evaluation of Outcomes

#### Quantitative Assessments

Via the NeW-I platform, both intervention and control group participants fill out a sociodemographic form at baseline and are then assessed on a battery of self-reported standardized and validated measures across 5 time points. The primary outcome measure is the participants’ quality of life, as measured by the Kemp Quality of Life scale (KQOL) [58]. Secondary outcomes are assessed using (1) a modified version of the Functional Assessment of Chronic Illness Therapy - Spiritual Well-Being scale (FACIT-Sp-12) [59], (2) the Herth Hope Index (HHI) [60], (3) Patient Health Questionnaire – 9 [53], (4) the Burden Scale for Family Caregivers-Short (BSFC-s) [61], (5) the Inventory of Social Support (ISS) [62], and (6) a modified version of the Brief Grief Questionnaire (BGQ) [63] (Table 4).

**Table 4 table4:** Quantitative outcome measures.

Measure	Number of items	Rating scale; factor
Kemp Quality of Life scale	1	7-point Likert scale; 1 factor
Functional Assessment of Chronic Illness Therapy - Spiritual Well-Being (adapted version)	12	5-point Likert scale; 3 factors: meaning, peace, and faith
Herth hope index	12	4-point Likert scale; 1 factor
Patient Health Questionnaire - 9 (also serves as a screening assessment)	9	4-point Likert scale; 1 factor
Burden Scale for Family Caregivers-Short	10	4-point Likert scale; 1 factor
Inventory of Social Support	5	5-point Likert scale; 1 factor
Brief Grief Questionnaire (adapted version)	5	3-point Likert scale; 1 factor

Assessment for both intervention and control groups takes place at 5 time points: baseline (time point 1), immediately after completion of the intervention or control protocol (time point 2), 1 month after completion of the intervention or control protocol (time point 3), 3 months after completion of the intervention or control protocol (time point 4), and a final follow-up 6 months after completion of the intervention or control protocol (time point 5). Participants receive an automated notification on their phone app and email each time an assessment set becomes available to them. For each completed assessment, participants receive a voucher worth Singapore $30 (approximately US $21).

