#### Acceptability and Feasibility Study

To evaluate the acceptability and effectiveness of NeW-I, all intervention participants are invited to participate in a semistructured interview at the completion of all intervention components at time point 2, which explores the impact of the intervention, aspects of the intervention found to be helpful, aspects of the intervention found to be unhelpful and how they could be improved, challenges encountered in completing the intervention, and scope for enhancing intervention usability. To assess the feasibility of implementing and delivering NeW-I, the research team maintains an audit trail of the time needed to provide feedback to participants and restructure their narrative writing; deviations from the intervention protocol (if any); uncompleted interventions and their reasons; and NeW-I therapists’ perceptions of competence, observations of participants’ experiences and responses, and difficult or deviant cases. All feedback provided to participants will be vetted by at least two members of the research team for data monitoring, quality, and safety assurance.

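### Every post-baseline assessment and the acceptability interview are dated from completing the writing protocol, with none scheduled for parents who stop early, so the intention-to-treat analysis risks resting on completers' outcomes

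*Protocol article*

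**What the plan says.** Quantitative Assessments lists five time points. The first is baseline. The other four share one anchor. The second falls "immediately after completion of the intervention or control protocol (time point 2"). The third and fourth are set one month and three months from that same event, and the last is "a final follow-up 6 months after completion of the intervention or control protocol (time point 5").

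The Quantitative Data section under Data Analysis compares the groups over all five, "with time point 2 being the primary time point of comparison". It adds: "The intention-to-treat principle will be followed in the data analysis". The main analysis is a mixed model on all available data, with multiple imputation as a sensitivity analysis.

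For acceptability, "all intervention participants are invited to participate in a semistructured interview at the completion of all intervention components at time point 2". The same section has the team keep an audit trail that covers interventions left unfinished and why.

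Study Design and Hypotheses predicts that "intervention participants who successfully complete NeW-I will experience an enhanced quality of life". Research Synopsis and Implications, in the Discussion, repeats the condition of completion.

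Two rules remove parents during the study. Under App and Intervention Procedure, a parent who has been randomised but does not start writing within 3 days is excluded, subject to a single 7-day concession. Under Sample, a parent who no longer meets the inclusion criteria is excluded, and data gathered up to then are kept and analysed.

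**The concern.** Intention to treat needs outcomes sought from everyone randomised, whether or not they did the sessions. Here the clock for every post-baseline measurement starts at an event that a parent who stops after session 1, 2 or 3 does not reach. Followed as written, the schedule gives that parent no time point 2, which is the primary comparison, and no time points 3 to 5.

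Completion happens after randomisation and may depend on what a parent was asked to write. The intervention asks about the burdens of caring for a seriously ill child. The control group is asked in weeks 1 and 2 about an average day and the past week. Unequal stopping is therefore plausible, though not established.

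The interview raises the same problem for the feasibility aim. Its topics include what was unhelpful and what made completion difficult, yet as timed these questions reach only parents who finished. That evidence is meant to inform a full-scale protocol.

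**Working it through.** **1. The plan's own figure.** From Sample Size Calculation: 25 per arm and 30% attrition. 25 / (1 − 0.30) = 35.7, rounded up to 36 per arm, or 72 in total. This attrition step reproduces. The 25 per arm comes from a cited source, and this point does not turn on it.

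**2. What a parent who stops early is scheduled for.**

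| Item | Trigger in the article | Date given for an early stopper |
|---|---|---|
| Time point 1 | Before randomisation | Already collected |
| Time point 2 (primary) | Completion | None |
| Time points 3, 4, 5 | 1, 3, 6 months after completion | None |
| Interview (intervention arm) | Completion of all components | None |
| Audit trail | Kept by the team | Reasons recorded, not the parent's own account |

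**3. How many parents this could affect.** The stopping fraction *s* is not given. The 30% is attrition at follow-up, so using it for early stopping is an assumption, and a range is shown.

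| *s* | Without scheduled follow-up, 72 × *s* | Completers per arm, 36 × (1 − *s*) |
|---|---|---|
| 10% | 7.2 (about 7) | 32.4 (about 32) |
| 20% | 14.4 (about 14) | 28.8 (about 29) |
| 30% | 21.6 (about 22) | 25.2 (about 25) |
| 40% | 28.8 (about 29) | 21.6 (about 22) |

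At 30%, the intervention arm would have 36 × 0.30 = 10.8, about 11 parents, with no scheduled interview.

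**4. What the analysis can recover.** If no stopper has a score at time points 2 to 5, every observed post-baseline value belongs to a completer. The mixed model and the imputation must then predict stoppers' outcomes from their baseline data and from how completers with similar baselines fared. No stopper's later score would exist to test that prediction.

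**5. Possible bias in the contrast (illustration, inputs assumed).** Suppose there is no true effect, both arms have the same overall mean *m*, and stoppers end up *g* SD worse than completers. With completer mean *c*, *m* = (1 − *s*)*c* + *s*(*c* − *g*) = *c* − *s g*, so *c* = *m* + *s g*. The completer contrast, intervention minus control, is then (*s*I − *s*C) × *g*.

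- 40% against 20%, *g* = 0.5: 0.20 × 0.5 = 0.10 SD in favour of the intervention
- same stopping, *g* = 0.25 and 1.0: 0.05 and 0.20 SD
- 20% against 40%, *g* = 0.5: −0.10 SD
- 30% in both arms: 0 for any *g*

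The 0.10 SD is half of the 0.2 effect size named in Sample Size Calculation. It refers to an unadjusted contrast. Baseline adjustment would remove whatever part of *g* the baseline data predict.

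**6. Different questions even without bias (illustration).** If completers gain 0.2 SD, stoppers gain nothing and stopping is equal, the effect in all randomised parents is 0.2 × (1 − *s*): 0.18, 0.16, 0.14 and 0.12 SD at 10%, 20%, 30% and 40%. The hypothesis as worded concerns the 0.2, whereas intention to treat concerns the smaller figure.

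**The case against.** The strongest reply is that this reads silence as a rule. No sentence says that early stoppers are not assessed. Completion of the protocol could mean the end of the protocol period, which is bounded: four weekly sessions counted from a defined first day, with one 7-day concession. The article says that assessments become available by automated notification, not that finishing session 4 unlocks them. It sends the reader to a procedures figure that is not shown, and a full protocol may hold the rule. This stands as far as it goes, and it is why the point is put as a risk and not as a fact about the trial's conduct.

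A reader might infer that the trial answers for completers only. The documents do not support that. The analysis is stated as intention to treat, stoppers' baseline scores stay in the mixed model, and imputation is added. What remains is that these methods cannot supply post-baseline information that was never scheduled.

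A reader might also infer that those who left can have no influence on the acceptability findings. That goes too far. The invitation is addressed to all intervention participants, and completers can also report that the intervention was unhelpful. The audit trail covers unfinished interventions, therapists' observations and difficult cases, and the qualitative analysis seeks out dissenting views. None of this replaces the stoppers' own account. It would also be wrong to put a percentage on overstated approval: the interview is semistructured and analysed phenomenologically, so no approval rate is planned.

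Finally, the hypothesis wording does not fix the analysis set. The efficacy objective in This Study and Objectives carries no completion condition. That is fair, but the two statements still need aligning.

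**Conclusion.** The concern holds in limited form. The article ties all four post-baseline assessments, including the primary one, and the interview to completion, and gives no date for a parent who stops early. Together with a hypothesis worded for completers, this conflicts with the stated intention-to-treat principle and needs reconciling.

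The size is uncertain. About 22 of 72 parents would be affected if all of the planned attrition were early stopping, and 7 to 29 over the 10% to 40% range. Some of the allowance reflects the end-of-life setting, so the true share may be lower. Bias in the contrast is not shown: it requires stopping to differ between arms and stoppers' outcomes to differ in ways that baseline does not explain. The stated sample size does not change.

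**What to change.** - **Assessments.** For every randomised parent, release time point 2 at a fixed time from randomisation: the scheduled end of the four weekly sessions, with a window for the 3-day start delay and the single concession. Counting four weeks as 28 days and adding both allowances, the window closes at 28 + 3 + 7 = 38 days. Release time points 3 to 5 at 1, 3 and 6 months after the scheduled time point 2, whether or not sessions were done. Randomisation is a better anchor than the first writing day, because parents who never start have no first writing day.
- **Interview.** Invite intervention-arm non-completers to the same interview at the scheduled time point 2.
- **Hypothesis.** Word it for all randomised parents, with completers as a secondary analysis.
- **Exclusions.** Reconcile the schedule with the late-start rule in App and Intervention Procedure and the loss-of-eligibility rule in Sample. Whether and how to follow parents after a child's death is for the study team; no rule is proposed here.

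The cost is small: a change to the app's release dates, some wording, and up to about 11 further interviews by the existing team if 30% stop. Some parents would answer time point 2 before using a concession week. Recruitment began in January 2019 and was ongoing, so a change now would mix two definitions of time point 2. The anchor used for each parent must therefore be recorded. If the full protocol already schedules early stoppers, saying so in the article settles the assessment part.
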